### Interventions

#### ETN Group

Thumbtack needle is in the shape of a thumbtack. It has a short body and a circular handle buried in a piece of round medical adhesive tape (Figure 2), which was produced by conductive material. In this trial, thumbtack needles of 0.25 × 2 mm size (Zhenxing, Hangzhou, China) will be used. Acupoints of Dazhui (GV14), bilateral Wangu (GB1 2), bilateral Jiaji at C4 and C6 levels, two Ashi points, and bilateral Houxi (SI3) will be selected in accordance with the theory of traditional Chinese medicine and the consensus of experts.

**Figure 2 F2:**
[figure not shown]
Electro-thumbtack needle and sham thumbtack needle. (1) Thumbtack needle or sham needle, (2) plastic plate, (3) adhesive tape, (4) needle, (5) blunt tip, (6) circular handle.

After sterilizing the skin around the acupoints, the acupuncturist will hold the handle of the needle between the thumb and forefinger, vertically insert the needle into the skin instantly, and adhere medical adhesive tape to skin. After that, the acupuncturist will setup the gel electrodes and the portable stimulation devices (Zhenxing, Hangzhou, China) (Figure 3) to the adhesive tape of all thumbtack needles, switch the mode to low-frequency and discontinuous wave, and adjust the current intensity from level 1 to an appropriate level, which the participant can tolerate. The acupuncturist will gently remove the medical adhesive tape and needles in 30 min.

**Figure 3 F3:**
[figure not shown]
Electric stimulation device and gel electrode.

Participants will receive three 30-min treatment sessions per week (ideally every other day) for 4 consecutive weeks after baseline assessment.

#### Sham ETN Group

We will use sham thumbtack needle specially designed to mimic the true needling. The sham thumbtack needle is 0.2 mm in length and has a blunt tip (rather than sharp) at the bottom. Other than these differences, the conductive surface and other structure of sham thumbtack needle are totally the same as true needle (Figure 2). In the sham ETN group, the blunt tip of needle will stay on the surface and not penetrate the skin, which avoids treatment effect to the largest extent and confuses the participants meanwhile.

Acupoints used in the sham ETN group are the same as those in the ETN group. Acupuncturist will first sterilize the areas of acupoints and then apply the sham needles on the surface of the skin. After assembling the same gel electrodes and portable stimulation devices as in the ETN group (Figures 3, 4), the acupuncturist will adjust the current intensity to level 1 (i.e., the minimum level). The minimal stimulus will last for only 30 s, after which the device will be turned down to cutoff the electric current. The duration of each session will also be 30 min. The frequency of treatment will be all the same as that in the ETN group.

**Figure 4 F4:**
[figure not shown]
ETN therapy or sham ETN therapy.

#### Neck Exercises

Standardized neck exercise of stretching and strengthening can help participants to relax the neck and acknowledge the appropriate posture. The exercise program consists of head retraction, neck extension, neck flexion, and rotation (Figure 5) (24). Each stretch must reach the maximum angle as possible and be hold for 5–10 s with a 10-s interval (15). When a participant is undergoing severe neck pain, he/she could conduct the exercise in clinostatism (24).

**Figure 5 F5:**
[figure not shown]
Neck exercise. **(A)** Head retarction. **(B)** Neck extension. **(C)** Neck flexion. **(D)** Neck rotation.

All participants will receive standardized neck exercise instruction at their first treatment session. The neck exercise will be performed at home later. A handbook with detailed illustrations to the exercise will be distributed to participants for guidance. Participants will be asked to perform the standardized exercise one time every day (20) (preferably in the morning) throughout the 4-week treatment. An exercise diary will also be distributed for supervision.

#### Concomitant Treatment

Any other therapy will be discouraged during this trial. Acetaminophen (sustained release type, 500 mg/T) will be provided as a rescue medication with the largest dose of 4 tablets per day for no more than 3 days in total in the condition of unbearable pain. Rescue medication or any other unexpected intervention will be recorded in detail. Proportion of participants and the total days taking rescue medication will be calculated and properly analyzed.

### Outcome Measures

#### Primary Outcome and Measurement

The primary outcome of this trial will be the proportion of participants with at least 50% decrease from baseline in the score of NRS-NP at the 4th week (25). The NRS-NP is a valid and reliable 11-point rating scale to assess the average intensity of neck pain during the last 3 days (26, 27). It is sensitive to small changes with a lower failure rate and can be delivered either graphically or verbally (26–28). The score of NRS-NP ranges from 0 (i.e., no pain at all) to 10 (i.e., the worst pain imaginable). Participants will be asked to circle out 1 of the 11 numbers to describe their pain. The scores of NRS-NP can be categorized into four degrees: 0 (i.e., no pain), 1–3 (i.e., mild), 4–6 (i.e., moderate), and 7–10 (i.e., severe). The reduction of 50% from baseline is regarded as golden standard of the NRS-NP to interpret significant clinically improvement (15, 28, 29).

#### Secondary Outcomes

Secondary outcomes include the proportion of participants with an at least 50% decrease from baseline in NRS-NP score at the 16th and 28th weeks; the changes from baseline in NRS-NP score at the 4th, 16th, and 28th weeks; and the proportion of participants with an at least 30% decrease from baseline in NRS-NP at the 4th, 16th, and 28th weeks. Other secondary outcomes include:

Changes in the Northwick Park Neck Pain Questionnaire (NPQ) percentage score from the baseline at the 4th, 16th, and 28th weeks.The proportion of participants with an at least 25% decrease in NPQ percentage score together with a “better” or “much better” at the 4th, 16th, and 28th weeks.

The NPQ is a validated questionnaire to assess the overall symptoms of neck pain (30). It contains 9 questions, the score of each ranging from 0 to 4, on the aspects of intensity, duration, numbness, sleep disturbance, and disability in carrying, watching television, working, social life, and driving. The total score of the 9 questions will be converted to NPQ percentage score (divided by 36 for people who drive and by 32 for those who do not), which ranges from 0 to 100%, and with higher scores indicating worse condition. A 25% decrease in NPQ percentage score and a “better” or “much better” for the 5-scale global effectiveness rating are both needed (31) to reach Minimal Clinically Important Difference (MCID).

(3) Changes from the baseline in Neck Disability Index (NDI) score at the 4th, 16th, and 28th weeks.(4) The proportion of participants with an at least 10-point decrease from the baseline in NDI score at the 4th, 16th, and 28th weeks.

The NDI is a frequently used instrument to evaluate the self-reporting functional status of patients with neck pain. It consists of 10 items concerning pain, headache, concentration, and daily obligatory activities. Each section is scored with an ordinal scale from 0 to 5, with a maximum score of 50 points (32, 33). Higher scores indicate greater functional limitation. The NDI has been translated into the simplified-Chinese version, which has been shown to have reproducibility, reliability, and validity (34). A 10-point decrease is required to achieve clinically important meaning (27, 35–37).

(5) The proportion of participants reported “much improved” or “very much improved” on Patient Global Impression of Change (PGIC) at the 4th week.

PGIC is a seven-point categorical scale to assess the participant's subjective satisfaction of the treatment (38). It is considered the most reliable instrument for trials concerning chronic pain (38–40). Participants are supposed to report their overall conditions in comparison with before the treatment using one of the following options: “very much worse,” “much worse,” “minimally worse,” “no change,” “minimally improved,” “much improved,” and “very much improved.” Those reported “much improved” or “very much improved” are considered responders of the intervention. It reflects not only the benefits of treatment but also the importance of the benefits for participants themselves (41).

(6) Expectation and belief.

Two questions will be elicited to assess the expectation of and belief in ETN, respectively. For expectation, participants will be asked “How do you think your neck pain will be in 4 weeks?” with the optional of “worse,” “unchanged,” “no idea,” “better,” and “much better.” For belief in ETN therapy, they will be asked “Do you think ETN therapy will be effective in treating chronic neck pain?” with the option of “not effective,” “little effective,” “not sure,” “effective,” and “very effective.” These questions will be elicited at the baseline.

#### Safety Assessment

Acupuncture-associated side effects such as bruising, dizziness, nausea, hematomas, infection, palpitations, or severe pricking pain [visual analog score (VAS) ≥ 4], and all other adverse events (AEs) irrelevant to acupuncture, will be carefully observed and recorded. Serious AEs (SAEs) will be reported to the Medical Ethics Committee of Guang'anmen Hospital within 24 h. After each session, the acupuncturist and outcome assessors will document adverse events and side effects if happens.

### Sample Size

The sample size calculation was based on the primary outcome of the proportion of participants with an at least 50% decrease from the baseline in average neck pain measured by NRS-NP at the 4th week. According to the previous literature, the response rate of TENS plus neck exercise for 4 weeks was reported to be 50% (15); therefore, we presume a 60% response rate of ETN plus neck exercise. For sham ETN plus neck exercise, we presume the response rate to be 38%. Accordingly, a two-tailed testing with an alpha of 0.05, a desired power set at 0.8, and an allowing dropout rate of 20% resulted in 90 participants needed in each group.

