### Recruitment

A total of 180 participants with chronic neck pain will be recruited in Guang'anmen Hospital *via* posters, WeChat, websites, and bulletin boards in hospital and communities. Diagnosis will be made by an orthopedist. Eligible participants will be officially enrolled only after signing a written informed consent, and all participants have the right to withdraw their consent later at any time.

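### The printed inputs (60% vs 38%, two-sided 0.05, 80% power, 20% dropout) need about 98 to 100 per group, not 90; with 90 per group the power is about 76%

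*Protocol article*

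**What the plan says.** The primary outcome is the "proportion of participants with at least 50% decrease from baseline in the score of NRS-NP at the 4th week" (Primary Outcome and Measurement), and the sample size is based on it. The Sample Size section gives every input:

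- ETN arm: "we presume a 60% response rate of ETN plus neck exercise".
- Sham arm: "For sham ETN plus neck exercise, we presume the response rate to be 38" (per cent).
- Test: "a two-tailed testing with an alpha of 0.05".
- Power: "a desired power set at 0.8".
- Result: "an allowing dropout rate of 20% resulted in 90 participants needed in each group".

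Allocation is 1:1 (Randomization and Allocation). The total matches 2 × 90: "A total of 180 participants with chronic neck pain will be recruited" (Recruitment). The Statistical Analysis section names the chi-square test or Fisher's exact test for responder proportions. No formula, software or continuity correction is given for the sample size calculation.

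**The concern.** All the inputs and the result are printed, so the calculation can be repeated without outside information, and the result does not follow. As worded, the 90 per group already includes the 20% dropout allowance, so the claimed 80% power should hold with 72 evaluable per group. It does not.

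At stake is the stated power for the primary comparison. It is the only reason given for enrolling 180 participants, and a non-significant result would be read against it. If the true power is lower, the risk of missing the assumed effect is understated.

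**Working it through.** **Inputs** (Sample Size section): p1 = 0.60, p2 = 0.38, difference d = 0.22, mean p = 0.49; two-sided alpha 0.05 (z = 1.96); power 0.80 (z = 0.8416); dropout 0.20; 1:1 allocation. Variance terms: p1(1−p1) + p2(1−p2) = 0.24 + 0.2356 = 0.4756, and 2 × 0.49 × 0.51 = 0.4998.

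**Step 1. Evaluable participants per group**

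- Pooled: n = [1.96·√0.4998 + 0.8416·√0.4756]² / 0.22² = (1.3856 + 0.5804)² / 0.0484 = 79.9, so 80.
- Unpooled: n = (1.96 + 0.8416)² × 0.4756 / 0.0484 = 77.1, so 78.
- Arcsine: n = 2(1.96 + 0.8416)² / h², with h = 2·arcsin√0.60 − 2·arcsin√0.38; this gives 79.7, so 80.
- Pooled with continuity correction: n′ = (n/4)·[1 + √(1 + 4/(n·d))]² = 88.7, so 89.

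**Step 2. Allowance for 20% dropout**

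| Formula | Evaluable | n / 0.8 | n × 1.2 (a common error) |
|---|---|---|---|
| Pooled | 80 | 100 | 96 |
| Unpooled | 78 | 98 | 94 |
| Arcsine | 80 | 100 | 96 |
| Continuity-corrected | 89 | 112 | 107 |

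If the unpooled figure is rounded only once, at the end, the results are 77.13/0.8 = 96.4, so 97, and 77.13 × 1.2 = 92.55, so 93. No entry is 90.

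**Step 3. Can 90 be reproduced?** Only by dropping a stated input:

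- One-sided test with continuity correction: 71.6, so 72 evaluable, and 72/0.8 = 90. This contradicts the two-tailed test.
- Two-sided test with continuity correction and no dropout allowance: 89. This contradicts the 20% allowance.

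The document does not say whether either was used.

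**Step 4. Power of the stated design.** 90 × 0.8 = 72 evaluable per group.

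- Pooled: z = (0.22·√72 − 1.3856)/√0.4756 = (1.8668 − 1.3856)/0.6896 = 0.698, power 75.7%.
- Unpooled: z = 0.22/√(0.4756/72) − 1.96 = 0.747, power 77.2%.
- Exact enumeration, uncorrected chi-square: 77.2%.
- Exact enumeration, Fisher's exact test: 71.7%.

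With no dropout (90 evaluable), the figures are 84.5% pooled, 83.4% exact chi-square and 79.4% Fisher.

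**Step 5. What would restore 80%?**

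- Dropout: pooled, 80 of 90 must be evaluable, so at most 1 − 80/90 = 11.1% may be lost. Unpooled, 78 of 90, so at most 13.3%.
- Effect: with 72 evaluable and a 38% sham rate, an ETN rate of 61% gives 79.5% pooled, so the rate would have to be slightly above 61%.

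**The case against.** The strongest points on the other side are these.

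- **Rounded inputs.** The rates are printed as whole percentages. At 60.4% vs 37.6%, the unpooled formula gives 71.5, so 72, and 72/0.8 = 90. This is possible, but it takes a favourable corner of the rounding range together with one particular formula. The rates are described as presumed, and nothing suggests they carried decimals.
- **Dropout may be smaller.** The primary endpoint falls at week 4, the end of treatment. Questionnaires can be completed by telephone or WeChat, including by those who stop treatment. Week-4 loss may well be below 20%, and with no loss power is above 80% for the chi-square test. This bears on what the trial may achieve. It does not support a statement that 80% power holds with 20% dropout allowed for.
- **Intention-to-treat with multiple imputation.** All 90 stay in the analysis, but imputation does not bring back lost information unless other data predict the outcome strongly. The Sample Size section claims no such gain.
- **Fisher's exact test.** With 72 per group the expected cell counts are about 35 to 37 (72 × 0.49 and 72 × 0.51), so Fisher's test would not normally be chosen. This stands: the 71.7% is a side figure, relevant only because the plan names the test without saying when it applies.
- **Precision.** Exact power does not rise smoothly with n, and the formulas differ by one or two points. That also stands, so the shortfall is best given as 3 to 4 points and the dropout limit as approximate.
- **Condensed article.** This would excuse a missing formula. It does not excuse printed inputs and a printed result that disagree.

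**Conclusion.** The statement is wrong as written. The printed inputs require about 98 to 100 randomised per group without continuity correction (97 if the unpooled figure is rounded once) and 112 with it. The stated 90 is short by about 8 to 10 per group, or 16 to 20 in total. At 20% dropout the design has about 76% power (75.7% to 77.2% for the uncorrected chi-square test, depending on the calculation), not 80%.

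This rests on the printed rates taken at face value, a two-sided 0.05 test, 1:1 allocation, and each dropout counting as a lost observation, which is how the Sample Size section treats it. The discrepancy is moderate. It does not bias the treatment comparison or invalidate the trial, but the power claimed for the primary outcome is not the power the design has.

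**What to change.** Keep 180 participants and replace the concluding sentence of the Sample Size section with one that is true of the design, for example:

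> With 90 participants per group and 20% dropout (72 evaluable per group), the power to detect 60% vs 38% at a two-sided 0.05 level is about 76%; power of 80% requires dropout of no more than about 11%.

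Name the formula used (these figures are from the pooled normal approximation without continuity correction), and remove the claim that the stated inputs result in 90 per group.

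The cost is one sentence and a stated power about 4 points lower. No participants are added and no procedure changes; the totals in the Abstract and in Recruitment stay as they are. The correction should be made before results are known.

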### Statistical Analysis

Data calculation will be performed using the SPSS software Ver.20.0 under the ITT principle. Baseline data before intervention will be analyzed to see if the two groups are comparable. The continuous data will be represented as mean ± SD deviation or median [interquartile range (IQR)]. Proportions of participants having clinically meaningful improvement will be analyzed using chi-square test or Fisher's exact test. Changes in the outcome measures from the baseline will be examined by using analysis of covariance for normally distributed data to exclude the possible impact on the effect by covariates of gender and work habits. Repeated-measures analysis of variance will be used if the data are not normally distributed. The Cochran-Mantel-Haenszel test will be used to analyze categorical data, which will be represented by percentages and case. We will use linear regression to discuss the association of participants' expectations and the treatment. Missing research data will be imputed by multiple imputations. For all statistical calculation, the significance level will be two-sided and set at 0.05. A *p* < 0.05 will be considered to indicate statistical significance.

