**Methods and Analysis:**

This is a sham-controlled, randomized clinical trial. A total of 180 subjects will be randomly allocated to either the ETN group or the sham ETN group. Treatment will be administrated three times a week for four consecutive weeks, with a 6-month follow-up. The primary outcome measure will be the Numerical Rating Scale for neck pain (NRS-NP) over a period of the 4 weeks. Secondary outcome measures include the Northwick Park Neck Pain Questionnaire (NPQ), Neck Disability Index (NDI), Patient Global Impression of Change (PGIC), patient expectation, and preference assessment. The chi-square test or Fisher's exact test will be used for proportions of participants having clinically meaningful improvement. Analysis of covariance or repeated-measures analysis of variance will be applied to examine changes in the outcome measures from baseline.

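### The primary responder outcome is worded differently in the abstract and is tested only by an unadjusted chi-square or Fisher test, which names no effect estimate to carry through the planned multiple imputation

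*Protocol article*

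**What the plan says.** **Primary outcome.** The abstract, under Methods and Analysis, states: "The primary outcome measure will be the Numerical Rating Scale for neck pain (NRS-NP) over a period of the 4 weeks". It gives no responder cut-off and no single time point. The section Primary Outcome and Measurement defines it as "the proportion of participants with at least 50% decrease from baseline in the score of NRS-NP at the 4th week". The Sample Size section agrees with that definition: "The sample size calculation was based on the primary outcome of the proportion of participants with an at least 50% decrease". Under Secondary Outcomes, the change in NRS-NP score at week 4 is listed as secondary.

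**Test.** The Statistical Analysis section says "Proportions of participants having clinically meaningful improvement will be analyzed using chi-square test or" Fisher's exact test, without a rule for choosing between them. A later sentence adds: "The Cochran-Mantel-Haenszel test will be used to analyze categorical data". No strata are named. Changes from baseline are to be analysed by covariance analysis with gender and work habits as covariates. No covariate is attached to the proportions.

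**Missing data.** The analysis follows intention to treat, and "Missing research data will be imputed by multiple imputations". No effect measure is named for the primary comparison.

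**The concern.** Two things do not fit together.

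First, the two wordings of the primary outcome lead to different methods within the article's own analysis section. A score over four weeks would go to covariance analysis or repeated-measures analysis of variance. A week-4 responder proportion goes to a test of proportions. A reader of the abstract alone could take a secondary outcome for the primary one.

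Second, the primary comparison is specified only as a choice between two tests, while the data will exist as several imputed sets. Rubin's rules combine an estimate and its variance. A chi-square or Fisher test by itself gives a statistic or a p-value per imputed set. The plan therefore names no quantity that passes directly from the imputed sets to one result, and none that would be reported as a size of effect with a confidence interval. The choice of test is also left open, and the two tests differ in power.

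**Working it through.** **Inputs.** Response rates of 60% (ETN) and 38% (sham), two-sided alpha 0.05, power 0.80, 20% dropout, 90 per group and 1:1 allocation, from the Sample Size and Randomization and Allocation sections. Evaluable at the allowed dropout: 90 × 0.8 = 72 per group.

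**The plan's own figure.** The pooled-variance formula is n = [1.96·√(2·p̄·(1−p̄)) + 0.842·√(p₁(1−p₁) + p₂(1−p₂))]² / (p₁−p₂)², with p̄ = (0.60 + 0.38)/2 = 0.49.
- First term: 1.96 × √0.4998 = 1.386.
- Second term: 0.842 × √(0.2400 + 0.2356) = 0.580.
- n = 1.966² / 0.22² = 79.9, so 80 per group. With 20% dropout, 80/0.8 = 100.

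The stated 90 is not reproduced. That is a separate matter. It enters here only because the power figures below are given at both 72 and 90 per group.

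**Does the choice of test matter?** Exact power is the sum, over all pairs of responder counts, of the two binomial probabilities for the pairs where the test rejects. The null rejection rate uses a common rate of 0.49.

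| Per group | Test | Power | Null rejection rate |
|---|---|---|---|
| 72 | chi-square (uncorrected) | 0.772 | 0.055 |
| 72 | Fisher | 0.717 | 0.037 |
| 90 | chi-square (uncorrected) | 0.834 | 0.045 |
| 90 | Fisher | 0.794 | 0.031 |

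Unrounded, the gap is 0.7717 − 0.7173 = 0.054 at 72 and 0.8338 − 0.7940 = 0.040 at 90. Part of it reflects how far Fisher stays below 5%. The chi-square is close to nominal, slightly above at 72 and slightly below at 90.

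**Is Fisher needed for sparse cells?** Smallest expected cell at 72 per group: 72 × 0.49 = 35.3 (the other is 72 × 0.51 = 36.7). To fall below the conventional 5, the overall response rate would have to be below 5/72 = 6.9% or above 93.1%. That is far from the planned rates.

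**Can a result be pooled?** A simulation used 10,000 runs, 90 per group, 20% of outcomes missing independently of response, and 20 imputations. The missingness mechanism and the number of imputations are assumptions; the protocol gives neither.

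| Pooled quantity | Power | Type I error |
|---|---|---|
| Risk difference, Rubin's rules | 0.759 | 0.050 |
| Chi-square statistic, D2 rule | 0.748 | 0.046 |

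Both routes work. The first gives an estimate and an interval as well as a p-value; the second gives only a p-value. The Fisher p-value has no standard combining rule.

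**Cochran-Mantel-Haenszel.** With a single stratum, its exact power is 0.772 at 72 and 0.833 at 90, practically the same as chi-square.

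**The case against.** The strongest reply is that little here is wrong. The abstract lists outcomes by instrument, and the Methods and the Sample Size section agree on the responder definition, so the operative endpoint is clear. Chi-square or Fisher is conventional wording for all responder proportions, including secondary ones that may be sparse. With expected cells near 35, convention would select chi-square and the power gap would not arise. An unadjusted test of a randomised binary endpoint is valid. The combining rule is commonly left to an analysis plan, which is not shown. The statisticians are blinded, and allocation is revealed only after the analysis, which limits choosing a test for its result.

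Most of this stands, and it keeps the point modest. It does not remove it. The article itself fixes the primary method as a test without an estimate, leaves the choice of test open, and adds multiple imputation.

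Three stronger readings are tempting, and the documents do not support them.
- **None of the named tests can be pooled, so no single p-value is possible.** A chi-square statistic can be combined by D2, and the risk difference behind the same two-by-two table pools by Rubin's rules. The protocol does not mention or exclude either.
- **Cochran-Mantel-Haenszel is a third candidate for the primary endpoint.** The analysis section has a specific sentence for clinically meaningful proportions, and the abstract assigns those to chi-square or Fisher only. The general sentence can refer to other items, such as the expectation and belief questions.
- **Omitting covariates from the primary test is an error.** It is a missed opportunity only.

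**Conclusion.** The point holds as a recommended, low-cost improvement. The abstract and the Methods word the primary outcome differently. The primary proportion is assigned to an unadjusted chi-square or Fisher test with no selection rule, and no poolable effect estimate is named although the data will be multiply imputed.

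The measurable cost of ending up with Fisher is about 5.4 points of power at 72 per group and 4.0 points at 90, given the planned rates of 60% and 38%. If chi-square is used, as convention would suggest, that cost is nil. What remains is that no effect size or interval is specified for the primary result. The gain from adjusting for baseline NRS-NP is not quantified, because the protocol gives no figure for how strongly baseline predicts response.

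The abstract wording and the Cochran-Mantel-Haenszel sentence are editorial and would not justify the point alone. The substance is the single, estimable primary analysis.

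**What to change.** 1. Reword the abstract so that the primary outcome is the week-4 responder proportion defined in Primary Outcome and Measurement.
2. Name one primary analysis: logistic regression of week-4 response on treatment and baseline NRS-NP, plus the plan's own covariates of gender and work habits.
3. Impute the NRS-NP score rather than the yes/no response, and derive response in each imputed set. Compute the marginal risk difference and its standard error in each set, pool by Rubin's rules, and report it with a 95% CI.
4. Keep the unadjusted chi-square as a sensitivity analysis, stating how it is combined over imputations (for example D2). Drop Fisher for this endpoint.
5. State that Cochran-Mantel-Haenszel applies only to other categorical items.

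The cost is about a paragraph of wording and modest extra programming, mainly for the standard error of the marginal risk difference. No additional data are needed for the baseline adjustment, since NRS-NP is already measured at baseline.

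### The ANCOVA of the continuous secondary outcomes names gender and work habits as covariates but not the outcome's own baseline score, which costs precision and leaves chance baseline imbalance uncorrected

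*Protocol article*

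**What the plan says.** In the protocol article, Statistical Analysis: "Changes in the outcome measures from the baseline will be examined by using analysis of covariance for normally distributed data", and the stated purpose of the adjustment is "to exclude the possible impact on the effect by covariates of gender and work habits". No other covariate is named.

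The fallback is given in the next sentence: "Repeated-measures analysis of variance will be used if the data are not normally distributed". It has no stated baseline covariate. The abstract (Methods and Analysis) repeats the choice of methods without covariates: "Analysis of covariance or repeated-measures analysis of variance will be applied to examine changes in the outcome measures from baseline". The only other use of baseline values in the analysis section is a comparison of the groups: "Baseline data before intervention will be analyzed to see if the two groups are comparable".

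The outcomes concerned are listed under Secondary Outcomes: "the changes from baseline in NRS-NP score at the 4th, 16th, and 28th weeks", "Changes from the baseline in Neck Disability Index (NDI) score at the 4th, 16th, and 28th weeks", and the NPQ percentage score at the same weeks. That makes three scales at three time points, nine comparisons in all. The primary outcome is of another kind: "The primary outcome of this trial will be the proportion of participants with at least 50% decrease from baseline in the score of NRS-NP". As a proportion, it is tested by chi-square or Fisher's exact test.

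**The concern.** A change score fixes the slope of follow-up on baseline at 1. The true slope is usually below 1, and the group that happens to start higher then tends to fall further whatever the treatment does. Part of a chance baseline difference therefore passes into the estimated treatment effect. The baseline score also leaves in the residual some variance that it could have explained.

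Gender and work habits can stand in for the baseline score only so far as they correlate with it. A comparability check at baseline describes imbalance but corrects none of it. Randomization and Allocation describes fixed blocks at 1:1 and mentions no stratification by baseline pain, so nothing described in the article limits such imbalance. At stake are the width of the confidence intervals for the nine change-score comparisons and how far each can be read without worrying about the groups' starting levels.

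**Working it through.** **Plan's own figure.** There is none on this point. The one design figure, 90 per group in Sample Size, belongs to the binary primary outcome. It is used here only to get completers: 90 × (1 − 0.20) = 72 per arm.

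**Inputs that are assumptions.** The article gives neither the baseline-to-follow-up correlation ρ nor any SD. I take ρ = 0.3, 0.5, 0.7 and k = follow-up SD ÷ baseline SD = 1, 1.25, 1.5. Gender and work habits are ignored.

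**Variance.** In units of the baseline variance, and apart from the common factor 2/n:
- change score without baseline: 1 + k² − 2ρk
- with baseline as covariate: k²(1 − ρ²)
- ratio R = k²(1 − ρ²) / (1 + k² − 2ρk)
- proportion saved, 1 − R = (1 − ρk)² / (1 + k² − 2ρk)

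The saving is never negative. It is zero only when ρk = 1, that is, when the true slope equals the slope that the change score assumes. At k = 1, R reduces to (1 + ρ)/2.

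| k | R at ρ = 0.3 | R at ρ = 0.5 | R at ρ = 0.7 |
|---|---|---|---|
| 1 | 0.65 | 0.75 | 0.85 |
| 1.25 | 1.422/1.8125 = 0.78 | 1.172/1.3125 = 0.89 | 0.797/0.8125 = 0.98 |
| 1.5 | 2.0475/2.35 = 0.87 | 1.6875/1.75 = 0.96 | 1.1475/1.15 = 1.00 |

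The variance cut is thus 35%, 25%, 15% at k = 1; 22%, 11%, 2% at k = 1.25; and 13%, 4%, 0% at k = 1.5.

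In power terms at k = 1, a change-score comparison that had 80% power would have Φ((1.960 + 0.842)/√R − 1.960), or about 94%, 90% and 86%. This is only an illustration, because none of these outcomes was used to size the trial.

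**Chance imbalance.** With 72 per arm the standard error of the baseline difference is √(2/72) = 0.167 baseline SD. A difference of 1.96 standard errors is 0.327 SD. It shifts the change-score estimate by −(1 − ρk) × 0.327 baseline SD:

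| k | ρ = 0.3 | ρ = 0.5 | ρ = 0.7 |
|---|---|---|---|
| 1 | −0.23 | −0.16 | −0.10 |
| 1.25 | −0.20 | −0.12 | −0.04 |
| 1.5 | −0.18 | −0.08 | +0.02 |

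With baseline in the model the shift is about 0.

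**Simulation check** (10,000 trials, 72 per arm, ρ = 0.5, k = 1). The variance ratio was 0.752 against a theoretical 0.75. The slope of the estimate on the baseline difference was −0.51 for the change score and −0.01 with baseline adjusted. Both estimators averaged about zero when the true effect was zero.

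**The case against.** **The article is condensed and the full plan may include baseline.** This is possible, and an article that said only ANCOVA would leave the matter open. This one states what the adjustment is for and names the covariates, and the baseline score is not there. Its SPIRIT table also answers No to the item on additional analyses, which covers adjusted ones. The objection lowers certainty about what will be done. It does not make the printed covariate list a good one.

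**The saving depends on more than the correlation.** This stands. The 15–35% range needs equal SDs. For NRS-NP that is doubtful: entry at 4 or more narrows the baseline spread, while follow-up can run from 0 to 10, with 38% to 60% of patients expected to halve their score. NPQ and NDI have no entry cut-off, so equal SDs are more plausible there.

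**Stronger readings that the documents do not support.**
- A reader might infer that selecting patients on a high NRS-NP makes the case stronger through regression to the mean. That is not generally true. If the qualifying score is itself the baseline, truncation weakens the correlation of change with baseline. With an assumed mean of 5, SD of 2 and ρ of 0.5 before selection, a cut at 4 moves it from −0.50 to −0.37 and R from 0.75 to 0.86. It strengthens, to −0.54 in the same setting, only if baseline is measured separately. The recall periods differ (7 days at entry, 3 days for the outcome), but the article does not settle which applies.
- A reader might infer systematic bias. Under 1:1 randomization the change-score estimate is unbiased on average; the bias is only conditional on the imbalance that occurred. The type I error rate is not threatened.
- A reader might turn the variance saving into a smaller trial. The sample size rests on the responder proportion, so no such link exists.

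**Conclusion.** The point holds as a costless improvement to the nine continuous secondary comparisons. The plan names covariates for a change-score ANCOVA and leaves out the baseline score, which is usually the most useful one and is already needed to compute the change. The consequences are lost precision and sensitivity to chance imbalance.

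The gain is material for NPQ and NDI if their SDs are similar at baseline and follow-up, and it may be small for NRS-NP. Those statements rest on assumed correlations of 0.3 to 0.7 and SD ratios of 1 to 1.5, which the article neither gives nor contradicts. Apart from one degree of freedom, adjustment does not do worse at any of these values. The primary result, the responder and PGIC outcomes and the sample size stand as they are.

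**What to change.** In Statistical Analysis, state that each continuous outcome (NRS-NP, NPQ, NDI) will be analysed by ANCOVA with its own baseline score as a covariate, in addition to gender and work habits. Carry the same baseline covariate into the planned repeated-measures analysis, with the post-baseline visits as the repeated responses.

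The endpoint can remain change from baseline: once baseline is in the model, the treatment effect is the same whether change or follow-up score is the response.

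The cost is one degree of freedom per model. No new data, visits or patients are needed. The change can be fixed in writing before allocation is revealed, which Data Management and Quality Control places after the statistical analysis is complete.
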